#### **7.1.2.10 Visit 11-16, family meeting (week 28, 32, 36, 40, 44 & 48)**

Registrations include (all children):

- Weight
- Height
- Dietary instruction
- Adverse events & concomitant medication

#### **7.1.2.11 Visit 17, CID 4, end of intervention period 2 (week 52)**

This family meeting will register the following parameters:

- Anthropometric measures including:
  - Weight (all children)
  - Height (all children)
  - Waist/hip (overweight children only)
  - Body composition (DEXA/bioimpedance) (overweight children aged >12 years only)
- Dietary instruction (adherence) (all children)
- Fasting blood samples (all children)
- Adverse events & concomitant medication (all children)
- BP (overweight children only)
- 3-day diet record (overweight children only)

#### **7.1.2.12 Visit 18, family follow-up meeting (week 104)**

Registrations include:

- Weight (all children)
- Height (all children)
- Waist/hip (overweight children only)

- Dietary instruction (adherence) (all children)
- Adverse events & concomitant medication (all children)

#### **7.1.2.13 Early termination (overweight children only)**

The registrations include (listed by priority):

- Date and reason for discontinuation (all children)
- Adverse events & concomitant medication
- Physical examination including BP (only if early termination is due to adverse event)
- Weight
- Body composition (DEXA-scanning/bioimpedance)
- Blood samples
- Diet registration (3 days)
- Waist/hip measurement
- Nutritional counselling

There will be a maximum volume of 25 ml blood taken on each CID day from children.

## **7.2 METHODS OF PRIMARY EFFECT PARAMETERS**

### **7.2.1 BODY WEIGHT**

Weight will be recorded to the nearest 0.1 kg. On CID 1-4, the subject must only be wearing underwear and weight should be measured in the morning in a fasting condition and with an empty bladder. At all other visits, the only requirement is that subjects should be weighed without coat & shoes. The weight will be recorded in source data at each visit using the same (or similar) calibrated scale.

### **7.2.2 HEIGHT**

Height will be measured with a wall-mounted stadiometer to the nearest 0.5 cm without shoes. Height will be measured for adults once at screening, and at each visit for children.

### **7.2.3 BODY COMPOSITION**

Body composition will be determined for adults and overweight children 4 times during the study, on CID 1-4, by DEXA or bioimpedance

A DEXA scanner (Lunar Radiation Co., Madison, Wisconsin, USA) will be used to determine lean tissue mass (LTM), fat mass (FM), bone mineral content (BMC) and total body weight (TBW). All scans will be performed using the appropriate scan velocity, depending on body weight and sagittal height. The expected scan time is 5-10 min. The subjects will receive 0.04 – 0.08 mrem of radiation pr. scan.

All subjects will be scanned in a fasting condition and only wearing light clothing. The total scan area will measure 61 cm x 196 cm. For subjects exceeding the grid, DEXA scans will be performed by excluding the outermost part of the arm and/or the thigh.

The subjects will be wrapped in a broad belt, made of coarse tightly woven cloth and closed using Velcro straps to maintain their position during the scan.

The same (or similarly competent) scan-operator will be used throughout the study.

The same scan-analyzer will be used throughout the study, to avoid variation in analysis of the scan results. Quality control and calibration check using the Lunar Aluminum Spine Phantom (LSP) will be performed at least once a week.

DEXA subject information will be handed to the subjects.

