Primary outcome measures for adults are body weight loss maintained (kg), change in body composition, proportion of subjects maintaining > 0, 5 and 10% weight loss, and drop-out rate. Other non-clinical primary measures are to identify biological and psychological traits that determine the family's and individual's responses to the dietary interventions. Secondary end-points are reduction in abdominal obesity, changes in risk factors of type-2 diabetes and CVD and appetite/satiety hormones, and changes in physical activity. Clinical measurements will include in addition the identification and quantification of adipose tissue mRNA and peptide biomarkers. Primary outcome measures for children are changes in the proportion of overweight and obese children at 6 mo, and changes in BMI, and % whole body fat. Secondary end-points for overweight children are reduction in abdominal obesity, changes in waist-hip circumference ratio and blood parameters and changes in physical activity. A sub-study (described below) will assess the effect and safety of the high protein diet in children and adolescents. Dietary effects on bone and kidney health will be assessed and primary safety end-points will include changes in urinary and blood proteins, such as albumin and creatinine.

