*Ad libitum* diets with high protein content have been shown to enhance satiety (9;10) and increase thermogenesis (11) in a number of smaller studies, and also produce better weight control and weight loss than diets in which the protein is replaced by carbohydrate (12;13). These high-protein diets are challenging the current recommendations (14) and need to be evaluated for efficacy and safety in a large, long-term, strictly controlled intervention trial (13). The Institute of Medicine (15) has recently increased the recommended acceptable daily protein intake for adults to 10-35% caloric intake and for children (aged 4-18) to 10-30%. A previous 6-month study found that a fat-reduced diet with high compared to normal protein enhanced weight loss and provided a greater reduction in intra-abdominal fat stores (12). However this pilot study did not have the statistical power to assess weight differences between groups after 12 months due to inadequate numbers of subjects (16). Moreover, adverse effects of high protein diets on renal function in healthy individuals have not been clearly established to date, and effects on bone are unclear (13). The safety and tolerability of a high protein diet in different age groups thus requires clarification, in particular in children; this will be exerted in the current study.

The rapid increase in childhood obesity which currently affects all European countries is of particular societal concern today. This study is novel because it focuses on the whole family. The aim is to identify the diet most effective for protection against weight gain and weight regain in a susceptible population of obese and overweight individuals and their children. Investigating the diet within the whole family should encourage overweight children to lose weight; indeed some studies have demonstrated that the family based approach to body weight management is most effective for weight loss. In addition the diet most beneficial for risk factors of CVD and type-2 diabetes also

requires clarification (5;14). The uncertainty about the optimal diet composition for the prevention and treatment of obesity is a public health problem which needs to be addressed by a large long-term randomized intervention trial. This is the background for the proposed dietary intervention study, which hopefully will contribute to the knowledge in this area and provide valid evidence that may help decision makers to make appropriate dietary recommendations.

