#### 1. 8 week LCD dietary period

The energy restricted LCD diet (for adults only) will consist of 800-1000 kcal/d and the target macronutrient composition of the diet will be 15-20% of total energy from fat, 35-40% from protein and 45-50% from carbohydrate. No energy restriction will be imposed for the children in the enrolled families. During this period, subjects will attend approx. 6 group meetings at the Department where their body weight, adverse events (AE) and concomitant medication will be registered and dietary and behavioural instructions will be given.

Before entering intervention period 1, adult subjects visit the Department for CID 2. This will again include anthropometric measurements, BP, blood sample and 24-h urine collection, fat biopsy, OGTT, analysis of body composition (DEXA scan), and completion of lifestyle/behavioural questionnaires. Families where at least one parent achieves a  $>8\%$  weight loss will be randomised to one of the 5 dietary arms.

Subgroup a will complete a 7-day food record and undergo BMR and DLW measurements, have physical activity measured by use of a pedometer and have a meal test.

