### **5.3 PROCEDURE FOR EXCLUSION/DISCONTINUATION DURING THE STUDY**

A subject will be removed from the study treatment based on their own decision or if the investigator finds it medically necessary.

If any child or adult refuses to follow dietary instruction after starting the intervention, the other family members will still be allowed to continue in the study. However, if refusal (by adult or overweight child) occurs before the start of the LCD diet, then the family will not be included in the study.

When a subject decides to discontinue participation in the study, he/she should always be contacted in order to, if possible, obtain information about the reason(s) for discontinuation. Whenever possible, the subjects should return for an unscheduled visit at the time of or soon after discontinuation.

The following procedures should be performed at an unscheduled visit:

- Date of discontinuation
- Reason for discontinuation
- Adverse events
- Recording of any new concomitant drug therapy or any changes to ongoing concomitant drug therapy since last visit, any pharmacological treatment established prior to entrance in this study will be maintained as long as ethically possible
- DEXA scan or bioimpedance (body fat mass, body lean mass)
- Body weight
- Blood pressure
- Waist/hip and sagittal measurements
- Blood sample
- Compliance Questionnaire

Subjects may also be withdrawn from the study because of severe protocol violations.

These subjects will not be included in the analysis and will permanently be dismissed from the study. Reasons for dismissal should be carefully recorded in the source data.

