#### **7.1.1.7 Visit 9, CID 2 (individual family meeting) (week 0)**

This family meeting (children participation is preferred but not required) following randomisation will register the following parameters:

- Anthropometric measures including:
  - Weight
  - Waist/hip and sagittal
  - Body composition (DEXA/bioimpedance)
- BP
- Fat biopsy
- Fasting blood samples
- OGTT & VAS scores
- End of day/compliance questionnaire
- Functional questionnaire
- Attitudinal/psychosocial questionnaire
- Food choice questionnaire
- Dietary instruction
- Adverse events & concomitant medication

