#### **7.6.3 SUB-STUDY FOR SAFETY ASPECT OF HIGH-PROTEIN DIET IN CHILDREN AND ADULTS**

This specific protocol will assess the potential risks associated with the high protein diet in both children and adults and will examine potential dietary effects on growth and metabolism in children and adolescents. Potential adverse effects on urinary calcium loss, bone loss or renal function will be assessed. The concentrations of serum urea (carbamide), albumin, osteocalcin and creatinine, and urinary albumin, creatinine and U-NTx will be measured in all intervention children on CID 1, 3 and 4. Serum urea and creatinine, and urinary albumin will in addition be measured on CID 2. Serum urea and urinary albumin, creatinine and U-NTx will also be measured in adults on CID 1, 3 and 4. The safety issue will also be addressed at follow-up (week 104) and the general health status of both children and adults will be assessed and certain parameters (e.g. height and weight in children) again measured. Any observed adverse effects (this applies to both children and adults) will be reported to the Ethical Officer in the DiOGenes Project Board ([name] [name], Director of the Institute for Bioethics, Department of Caring Sciences of the University of Maastricht, Netherlands) and action will be taken based on the decisions taken by the Project Board.

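### DEXA bone mineral content, the protocol's only measure of bone mass, is given no role in the bone-safety assessment, which lists turnover markers alone

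*Protocol*

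**What the plan says.** The aim is stated more than once. The protocol's background (Section 2) says of high-protein diets that "effects on bone are unclear". The synopsis (Aims) says "Dietary effects on bone and kidney health will be assessed". Section 7.6.3 says "Potential adverse effects on urinary calcium loss, bone loss or renal function will be assessed".

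Section 7.6.3 then fixes the measures by analyte and visit. The bone items are osteocalcin and U-NTx in children, and U-NTx in adults, all at CID 1, 3 and 4. The extra CID 2 measurements in that section are serum urea, serum creatinine and urinary albumin; none is a bone marker.

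Section 7.2.3 says "Body composition will be determined for adults and overweight children 4 times during the study, on CID 1-4, by DEXA or bioimpedance", and that the DEXA scanner "will be used to determine lean tissue mass (LTM), fat mass (FM), bone mineral content (BMC) and total body weight (TBW". Section 3 names DEXA for adults at all four CIDs; for the visit before intervention period 1 it lists "fat biopsy, OGTT, analysis of body composition (DEXA scan), and completion of lifestyle/behavioural questionnaires". The visit schedule places this at "Visit 9, CID 2 (individual family meeting) (week 0". The visit lists in 7.1 allow either DEXA or bioimpedance. In children they limit body composition to overweight children older than 12, a limit that Sections 3 and 7.2.3 do not state.

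BMC is mentioned in only two places: the abbreviation list and 7.2.3, which falls under the methods for primary effect parameters. It is not named in 7.6.3, in the safety end-points of the synopsis, or in the outcomes of 8.2.2 and 8.2.3.

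**The concern.** Turnover markers describe how fast bone is being resorbed or formed at the time of sampling. They do not say whether mineral has been lost over the intervention. The protocol treats the effect of high protein on bone as an open safety question, and it schedules scans that measure bone mineral directly. As written, a conclusion on bone loss in adults would rest on one urinary marker, while a direct measurement from the same visits has no stated part in answering the question.

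Timing adds to this. U-NTx is not scheduled for adults at CID 2, so the listed adult bone measures include none at the start of the randomised diet. BMC would supply one.

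**Working it through.** The protocol states no figure for this point, so the check is a cross-reading of the schedule followed by a head count.

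**Adult bone-related measures by visit** (7.2.3 and Section 3 for BMC; 7.6.3 for U-NTx):

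| Visit | Timing | U-NTx | BMC, if scanned by DEXA |
|---|---|---|---|
| CID 1 | week -12 to -9, before the LCD | yes | yes |
| CID 2 | week 0, diet start | no | yes |
| CID 3 | week 26 | yes | yes |
| CID 4 | week 52 | yes | yes |

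Section 3 mentions a 24-h urine collection at CID 2, whereas 7.1.1.7 and 7.7.5 do not. This does not change the table, because 7.6.3 does not list adult U-NTx at CID 2 in any case.

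**What each measure supports.** A change in U-NTx from CID 1 to CID 3 or CID 4 spans the 8-week LCD as well as the randomised diet. A change in BMC from CID 2 spans the randomised diet only, and matches the adult covariate that 8.2.4 and 8.2.6 use for efficacy.

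**Head count.** The synopsis (Subjects) gives about 110 adults for randomisation to 5 arms and more than 80 expected at 12 months. Section 4.1 has two high-protein and two normal-protein arms. Assume equal arms and equal losses.

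- Completers: 80 / 5 = 16 per arm, and 2 x 16 = 32 per protein level.
- Randomised: 110 / 5 = 22 per arm, and 2 x 22 = 44 per protein level.

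So about 32 versus 32 adults could have BMC at both week 0 and week 52. At week 26 the number per protein level would lie between 32 and 44. Each adult on bioimpedance at either visit reduces the count.

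**Children.** 7.6.3 applies its markers to all intervention children. BMC could exist only in overweight children scanned by DEXA, and by the visit lists only in those older than 12.

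**The case against.** Three stronger readings are tempting, and the protocol supports none of them.

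*The BMC data will go unused.* This would be an inference from silence. BMC is listed under body composition in 7.2.3, change in body composition is a main adult outcome in 8.2.2, and 8.2.4 analyses main outcomes at weeks 26 and 52 with CID 2 as the adult covariate. BMC may well be reported by that route. What stands is narrower: an efficacy heading that does not name bone commits nobody to a BMC comparison as part of bone safety.

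*The protocol defines body composition so as to leave bone out.* Section 5.3 does give "DEXA scan or bioimpedance (body fat mass, body lean mass", but that is a checklist item for an unscheduled discontinuation visit and covers either device. The early-termination lists in 7.1.1.20 and 7.1.2.13 carry no such restriction. It does not define the outcome.

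*The adult bone comparison is invalid without a diet-start value.* It is not. CID 1 precedes randomisation and every adult follows the same LCD, so U-NTx at CID 3 or CID 4 adjusted for CID 1 is a sound randomised contrast. What may be lost is precision.

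It can also be said that the choice of scan outputs for the safety tables belongs in an analysis plan. That would hold if the protocol were silent on safety measures. Here 7.6.3 sets them out itself, and the list falls short of the aim in the same paragraph.

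The limits of BMC are real. Section 7.2.3 says that subjects too large for the scan grid have part of the arm or thigh left out, which truncates BMC in an obese population, and the part left out may alter as weight changes.

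**Conclusion.** The point holds as a gap between an aim and the measures assigned to it. The protocol undertakes to assess bone loss, lists only turnover markers, and gives no bone-safety role to its one measure of bone mass, which is also the only adult bone measure at week 0. The trial and its U-NTx comparison remain valid without any change; what is limited is what can be concluded about bone loss.

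The size is up to four BMC readings per scanned adult and the roughly 32 versus 32 paired adults counted above. That rests on 80 completers, equal arms and DEXA at both visits. It is a head count, not a statement of power: the protocol gives no standard deviation for BMC, so no interval width can be worked out, and parents in one family share a diet. The case for the change is that it is cheap and answers the stated question more directly, not that it is known to be decisive.

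**What to change.** Add BMC to the bone-safety list in 7.6.3.

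- **Adults:** compare BMC at CID 3 and at CID 4 between the high- and normal-protein arms by ANCOVA adjusted for CID 2 BMC, with a 95% confidence interval. Do not adjust the main comparison for weight change. It arises after randomisation and is the primary outcome (8.2.7), so adjusting could remove a bone effect that acts through weight and bias what remains. A weight-adjusted version may be shown only as a labelled supplementary analysis.
- **DEXA-scanned overweight children** (older than 12 by the visit lists): adjust for CID 1 BMC and for baseline age, sex and height. Do not adjust for height change, since growth is itself a possible diet effect under 7.6.3.
- **Data:** use DEXA values only, with the same scanned regions at each visit.
- **Keep** U-NTx and osteocalcin in the list.

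The cost is wording and analysis time; no visit, scan or radiation is added. The text should state the downsides: bioimpedance gives no BMC; subjects who exceed the grid have truncated values; the comparison rests on those who are rescanned; and normal-weight children and, by the visit lists, overweight children aged 12 or under are not covered.

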## **7.3 METHODS OF SECONDARY EFFECT PARAMETERS**

### **7.3.1 WAIST AND HIP CIRCUMFERENCE AND SAGITTAL MEASUREMENT**

The waist and hip circumference will be determined for adults and overweight children 5 times during the study, on CID 1-4, and during follow-up (week 104). Adults will also have sagittal measurements.

The circumference will be measured to the nearest 0.5 cm with the same tape, if possible, with the subject standing. The subject must only be wearing underwear. The waist measurement will be taken midway between the lower rib and iliac crest at the umbilicus. The waist circumference should be measured in a fasting condition in the morning and with an empty bladder. The subject should breathe normally and the measurement should be taken when the subject is breathing out. The hip circumference will be measured as the largest circumference in the area around the buttocks.

### **7.3.2 BLOOD LIPID PROFILE**

Blood lipids are determined on CID 1-4 for adults only.

Measurements of fasting total HDL, total LDL, VLDL cholesterol, total cholesterol and triglycerides are performed.

### **7.3.3 BLOOD COAGULATION FACTORS, HORMONES, PEPTIDES & OTHERS**

In adults, fasting blood samples for the analysis of coagulation factor VIIc, fibrinogen, C-reactive protein, adiponectin, ghrelin and other relevant peptides, hormones or markers of appetite regulation, body metabolism, inflammatory responses, or obesity related diseases will be taken on CID 1-4. Blood for analysis of various adipokines/cytokines and peptides will be taken on CID 1-3 (adults only), and blood for DNA extraction will be taken on CID 1.

In children, fasting blood samples for the analysis of glucose, insulin, Insulin-like Growth Factor-1 (IGF-1), IGF Binding Protein-3 (IGFBP-3) or other relevant markers for growth, appetite regulation, glucose homeostasis, cardiovascular risk etc. will be taken.

### **7.3.4 GLUCOSE SENSITIVITY**

An OGTT will be performed on adult subjects on CID 1-4. Each subject will take a load of 75 g glucose within a 5 min period. The subjects will remain semi-recumbent and resting throughout the procedure, and must fast (except for 1 dL of water) until completion of the test. Blood samples will be obtained for glucose and insulin at 0, 30, 60, 90 and 120 minutes after drinking the liquid glucose solution. The 0 and 60 min samples will also be analyzed for small and large-sized peptides (i.e. peptidomic/proteomic analyses).

Information about the OGTT-procedure will be given out to the subject. During the OGTT subjective appetite ratings will be made using Visual Analogue Scales (VAS).

### **7.3.5 BLOOD PRESSURE**

Systolic and diastolic BP will be recorded by an automatic device after 5-10 min while resting in a supine position at screening (visit 1), CID 1-4 and during follow-up (week 104) (adults) and on CID 1-4 (overweight children).

### **7.3.6 PHYSICAL ACTIVITY**

This is a 2. outcome measure therefore need to know – how often & what activity scheme used.

## **7.4 METHODS OF ADIPOSE TISSUE SAMPLING**

An adipose tissue sample will be taken on CID 1-3 and 3 days into the LCD diet (Subgroup b only). This will be analysed for mRNA content (genome wide transcriptomic analyses) by RTD line 2, coordinated by [name] (INSERM UPS U586, [name]).

## **7.5 SUBGROUP MEASURES**

### **7.5.1 METHODS FOR DLW ANALYSIS**

On CID 1-3 subjects will be dosed with doubly labelled water to estimate daily energy expenditure over 14 days. Urines will be collected before DLW dosing, at 2 and 4 hours post-dose and one aliquot at 11 am on days 13 and 14.

Subjects will receive a stable isotope dose of approximately 0.1g D2O (99%) and 1g H2 (10%) per kg body weight.

